**Methods/Design:**

The DASH after TBI study is an actively accruing, single-center, randomized, double-blinded, placebo-controlled, two-arm trial, where one group receives centrally acting sympatholytic drugs, propranolol (1 mg intravenously every 6 h for 7 days) and clonidine (0.1 mg per tube every 12 h for 7 days), and the other group, double placebo, within 48 h of severe TBI. The study uses a weighted adaptive minimization randomization with categories of age and Marshall head CT classification. Feasibility will be assessed by ability to provide a neuroradiology read for randomization, by treatment contamination, and by treatment compliance. The primary endpoint is reduction in plasma norepinephrine level as measured on day 8. Secondary endpoints include comprehensive plasma and urine catecholamine levels, heart rate variability, arrhythmia occurrence, infections, agitation measures using the Richmond Agitation-Sedation Scale and Agitated Behavior scale, medication use (anti-hypertensive, sedative, analgesic, and antipsychotic), coma-free days, ventilator-free days, length of stay, and mortality. Neuropsychological outcomes will be measured at hospital discharge and at 3 and 12 months. The domains tested will include global executive function, memory, processing speed, visual-spatial, and behavior. Other assessments include the Extended Glasgow Outcome Scale and Quality of Life after Brain Injury scale. Safety parameters evaluated will include cardiac complications.

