### Study endpoints

We collect baseline data regarding demographics, socioeconomic status, medical history, medication use, and injury characteristics and severity, according to the common data elements for TBI advocated by multiple agencies, including the National Institute of Neurological Disorders and Stroke. Also, we collect pathoanatomic data elements that encompass the Marshall CT classification, Rotterdam CT score, and other consensus-derived data elements [45,46].

Our current primary endpoint is plasma norepinephrine level on day 8. Within 1 h of enrollment and after treatment on day 8, blood is drawn for plasma catecholamine measures and a 24-h urine collection is started for urine catecholamine measures. Blood is collected into cooled heparinized tubes, which are immediately placed on ice until they are centrifuged at for 10 min at 3,000 rpm. Plasma is harvested and stored in tubes containing 40 mL of reduced glutathione (6%) at −20°C until it is assayed. Catecholamine concentrations are measured by high performance liquid chromatography using electrochemical detection with dihydroxybenzylamine as the internal standard [47]. Catecholamines measured include norepinephrine, epinephrine, dopamine, dihydroxyphenylglycol, dihydroxyphenylalanine, and dihydroxyphenylacetic acid.

Other physiologic measures of response for the DASH After TBI Study are HRV and related responses to autonomic cold pressor testing, daily physiologic measures (for example, temperature, blood pressure, heart rate, intracranial pressure), arrhythmia occurrence, infections, adverse and serious adverse events.

Additional secondary outcomes are twice daily measurements of the Richmond Agitation-Sedation Scale (RASS) and Agitated Behavior Scale (ABS) for TBI, daily medication use (anti-hypertensives, sedatives, analgesics, and antipsychotics), coma-free days, ventilator-free days, ICU LOS, hospital LOS, and in-hospital mortality.

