A long-term study component begins with a baseline neuropsychological evaluation performed at hospital discharge. In the Vanderbilt Multidisciplinary TBI Clinic at 3 and 12 months, neuropsychological tests cover global executive function, memory, processing speed, visual-spatial, and behavioral domains, in addition to the validated Extended Glasgow Outcome Scale (GOSE) and (Quality of Life after Brain Injury) QOLIBRI scales. The specific neuropsychological tests are as follows: Tower Test, Galveston Orientation and Amnesia Test, Numbers Reversed and Verbal Analogies from Woodcock-Johnson: Tests of Cognitive Abilities, Three Word Recall from Modified Orientation Amnesia Test, Story Retelling Immediate Subtest and Delayed Subtest from Arizona Battery for Communication Disorders of Dementia, Trail Making A&B, Stroop Test, Word Fluency, and Zoo Map from Behavioral Assessment of Dysexecutive Syndrome. Also, the Social Security Death Index is queried monthly for long-term mortality assessments.

Safety parameters collected throughout the study include cardiac complications such as dysrhythmia (for example, symptomatic bradycardia), myocardial infarction, and cardiac arrest. Serious adverse events are reported in a blinded fashion to the Data Safety Monitoring Board within 24 h.

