### Statistical analysis

All analyses will occur on an intention to treat basis and will be blinded to treatment assignment. Interim analysis is not planned, unless the sample size is expanded. The primary endpoint is post-treatment plasma norepinephrine level on day 8. The outcome is continuous and independent, while the exposure is dichotomous. To test for an association between post-treatment plasma norepinephrine level and treatment, we will use a Wilcoxon rank sum test statistic with the standard error determined empirically by the randomization method.

HRV linear analyses (frequency and spectral) will be performed. HRV spectral analysis will be performed to calculate very low frequency, low frequency (LF), and high frequency (HF) bands, with a LF/HF ratio calculation to understand sympathovagal balance. Understanding the limitations of spectral analysis, we will compute other HRV measurements including standard deviation of normal beat intervals and entropy.

For secondary outcome analyses, the Type I error probability will be adjusted to account for multiple comparisons. We will use Fisher’s exact test to compare categorical variables between the study groups (for example, RASS). GOSE will be compared using an ordinal approach of sliding dichotomy [50]; QOLIBRI, ventilator-free days, hospital LOS, and ICU LOS are continuous measures that will be analyzed the same as the primary endpoint. Mortality will be studied using Kaplan-Meier analysis and Cox Proportional Hazard Modeling. The raw test scores of the neuropsychological battery will be transformed into standardized scores based on mean and standard deviations of the normative sample with similar age and education levels (T-scores). These T-scores will be summarized using medians with interquartile ranges for continuous outcome variables, and frequencies or proportions for categorical outcome variables.

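### The multiplicity adjustment for secondary outcomes does not exempt harms, so arrhythmia and infections share alpha with the efficacy outcomes

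*Protocol article*

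**What the plan says.** Four places in the protocol article bear on this.

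- **Abstract, Methods/Design.** The secondary list opens: "Secondary endpoints include comprehensive plasma and urine catecholamine levels, heart rate variability, arrhythmia occurrence, infections, agitation measures". The same list ends with "coma-free days, ventilator-free days, length of stay, and mortality". Arrhythmia, infections and mortality are therefore expressly secondary. Safety parameters, meaning cardiac complications, come in a separate sentence at the end of that paragraph.
- **Study endpoints, other physiologic measures of response.** This list ends with "arrhythmia occurrence, infections, adverse and serious adverse events". The next paragraph begins: "Additional secondary outcomes are twice daily measurements of the Richmond Agitation-Sedation Scale".
- **Study endpoints, safety paragraph.** "Safety parameters collected throughout the study include cardiac complications such as dysrhythmia". Myocardial infarction and cardiac arrest are named as well, and serious adverse events go to the monitoring board in blinded form within 24 h. No test or error rate is given for these parameters.
- **Statistical analysis.** "For secondary outcome analyses, the Type I error probability will be adjusted to account for multiple comparisons". The same paragraph assigns Fisher's exact test to categorical variables and says: "Mortality will be studied using Kaplan-Meier analysis and Cox Proportional Hazard Modeling". It names no outcome as exempt.

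**The concern.** A multiplicity adjustment protects against false claims of benefit when many outcomes are tested. For a harm, the costly error is the opposite one, a missed signal. If harms sit in the same adjusted family as catecholamines, heart rate variability, agitation scales, medication use and lengths of stay, each added efficacy outcome raises the evidence needed to flag an excess of arrhythmia or infection.

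The article also gives rhythm disturbance two roles, as a secondary endpoint and as a safety parameter. Only the secondary role has an error rule.

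The article says that safety evidence is lacking, gives the investigation of safety as a purpose of the trial, and presents the trial as possible pilot evidence for a larger multicenter one. With 20 patients per arm there is little power for harms to begin with, and the adjustment lowers it further.

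**Working it through.** **The plan's own figures.** The article gives no number for the adjustment or for detecting harm. The relevant stated figure is the sample size, and it reproduces: a difference of 450 pg/mL, SD 416, two-sided alpha 0.05 and power 0.90 give 19 per arm by the noncentral t (power 0.9004). Allowing for 5% early mortality, 19 / 0.95 = 20 per arm.

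**Inputs for the illustration**
- From the article: 20 per arm, Fisher's exact test for categorical outcomes, nominal alpha 0.05.
- Assumed: Bonferroni, with threshold 0.05/k for k = 4, 10 or 20 tests; a control event rate of 5%; various treated-arm rates. The article states none of these.

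**Step 1: smallest excess over zero that is flagged.** For x events in one arm and none in the other, with 20 per arm, the two-sided Fisher p-value is

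p = 2 × C(20, x) / C(40, x).

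For x = 5: 2 × 15,504 / 658,008 = 0.047. In the same way, x = 7 gives 0.0083, x = 8 gives 0.0033 and x = 9 gives 0.0012.

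| Tests k | Threshold 0.05/k | Smallest excess flagged | p |
|---|---|---|---|
| 1 (no adjustment) | 0.05 | 5 v 0 | 0.047 |
| 4 | 0.0125 | 7 v 0 | 0.0083 |
| 10 | 0.005 | 8 v 0 | 0.0033 |
| 20 | 0.0025 | 9 v 0 | 0.0012 |

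With one event in the control arm, the treated arm needs 7 events at 0.05 and 9, 10 or 11 at k = 4, 10 or 20.

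**Step 2: chance of flagging harm.** Sum Bin(a; 20, control rate) × Bin(b; 20, treated rate) over all pairs with b > a and Fisher p ≤ 0.05/k.

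| Treated v control rate | k = 1 | k = 4 | k = 10 | k = 20 |
|---|---|---|---|---|
| 30% v 5% | 45% | 19% | 10% | 5% |
| 40% v 5% | 72% | 45% | 31% | 20% |

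**Step 3: smaller harms, no adjustment.** The chance of flagging is 17% for 20% v 5% and 7% for 15% v 5%. For harms of this size, the sample size is already the main limit.

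**Scope of the illustration.** It applies to outcomes compared as proportions, such as arrhythmia and infections. It does not apply to mortality, which the article assigns to Kaplan-Meier and Cox analysis.

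**The case against.** The strongest reply is that the article keeps safety apart. The abstract and Study endpoints both give cardiac complications their own statement, and the adjustment sentence covers secondary outcome analyses only. That stands for myocardial infarction, cardiac arrest and the other safety parameters: nothing places them under the adjustment. It does not clear arrhythmia and infections, which the abstract names as secondary. Arrhythmia also overlaps with dysrhythmia, for which no unadjusted comparison is promised.

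A reader might infer three stronger things that the document does not support.

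- **That adverse events are declared secondary outcomes.** They are missing from the abstract's list. Their secondary status follows only by implication, because the paragraph after theirs speaks of additional secondary outcomes.
- **That the plan makes a finding of harm depend on an adjusted p-value.** No such rule appears, and nothing says that non-significance will be read as safety. Serious adverse events reach the monitoring board whatever the adjustment. The effect is on the formal between-arm tests only.
- **That mortality should simply leave the adjusted family.** The Background cites retrospective evidence of a 4% to 23% absolute mortality advantage with beta-blockade, so mortality is also a hoped-for benefit. Outright exemption would allow an unadjusted benefit claim from 40 patients.

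It can also be said that a condensed article leaves details to an analysis plan that is not shown. That holds for the adjustment method and the number of tests, and their absence is not criticised here. The point is the scope that the article itself states, which covers secondary outcomes without qualification.

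**Conclusion.** The concern holds in a limited form. Arrhythmia and infections are named as secondary, the adjustment covers secondary analyses with no exemption for harms, and rhythm disturbance is also classed as safety. As written, the rule weakens the final between-arm comparison of these harms in a trial that is meant to inform safety.

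The direction of the effect does not depend on the assumptions, because any family-wise correction tightens the threshold. The size does. Under Bonferroni over 4 to 20 tests, the smallest flagged excess over zero moves from 5 v 0 to between 7 v 0 and 9 v 0, and the chance of flagging 30% v 5% falls from 45% to between 19% and 5%. These figures are illustrations and not properties of the plan. The loss matters for large harms; small ones would mostly be missed with or without the adjustment.

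**What to change.** In Statistical analysis, limit the adjustment to secondary claims of benefit. Then state the following:

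- Arrhythmia, infections, cardiac complications, and adverse and serious adverse events are safety outcomes. They are reported by arm as counts, with unadjusted risk differences and 95% confidence intervals.
- Non-significance for a safety outcome is not read as evidence of safety.
- Any claim of mortality benefit stays inside the adjusted family. Deaths are also reported by arm, with an unadjusted estimate and 95% confidence interval, for safety.

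Bring the endpoint lists in the abstract and Study endpoints into line, so that each of these events has one stated role, with mortality's two uses spelled out.

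The change is to wording only and adds no patients or data. Its downside is a higher chance of a false safety signal, which is usually the preferred error for harms.

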### Treatment delivery

Study drugs start within 48 h of injury but after plasma and 24-h urine catecholamine baseline measurements. Both drugs (or double placebos) are administered for 7 days. Propranolol is administered intravenously at a dose of 1 mg every 6 h, and doses are held for heart rate less than 60 bpm, mean arterial pressure less than 60 mmHg, or cerebral perfusion pressure less than 60 mmHg. Clonidine is administered at a dose of 0.1 mg per tube every 12 h, and is held for mean arterial pressure <60 mmHg, or cerebral perfusion pressure <60 mmHg. Administration of propranolol and clonidine, or of the double placebos, is staggered. If hemodynamic parameters are met while a patient is on pressors, drug delivery still occurs. Other aspects of study feasibility being documented are compliance with treatment delivery and reasons for withholding treatment.

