### Current sample size justification

Primarily, we expect plasma norepinephrine reduction after adrenergic blockade in severe TBI subjects. This continuous response variable will involve an independent control and experimental subjects with one control per experimental subject. In previous TBI studies [3,6], the baseline plasma norepinephrine level was 1,686 ± 416 pg/mL. If the plasma norepinephrine level decreases to 1,236 pg/mL after adrenergic blockade, then the true difference in the experimental and control means is 450 pg/mL. Using the Power and Sample Size Calculation program [49], we will need to study 19 experimental subjects and 19 control subjects to be able to reject the null hypothesis that the population means of the experimental and control groups are equal with a probability (power) of 0.9. The Type I error probability with testing this null hypothesis is 0.05.

If the absolute reduction of plasma norepinephrine using adrenergic blockade after severe TBI is only 300 pg/mL, and power is constant at 0.9 and the Type I error probability remains at 0.05, then we will need to study 41 patients per arm. Alternatively, if plasma norepinephrine is reduced by 600 pg/mL after intervention, then we will only need to study 11 patients per arm (Figure 3).

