**Figure 3 F3:**
[figure not shown]
**Current sample size *****vs. *****power for Δ plasma ****norepinephrine on day 8**.

Our center admits over 200 severe TBI patients per year, but given the strict eligibility criteria, and assuming a conservative 10% enrollment rate, we anticipate a 24-month total accrual time for 38 patients. An additional 12-month follow-up is required to fulfill all of the DASH After TBI Study aims. Lastly, despite exclusion criteria, we assume a 5% early mortality (<1 week) related to critical illness. Accordingly, our current sample size is 20 patients per arm or a total of 40 patients.

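### Fisher's exact test is named for RASS, a graded scale scored twice daily; it ignores the ordering and gives up power that the protocol's own rank test would keep

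*Protocol article*

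**What the plan says.** Under Study endpoints, the protocol article makes RASS a repeated measurement: "Additional secondary outcomes are twice daily measurements of the Richmond Agitation-Sedation Scale (RASS) and Agitated Behavior Scale (ABS) for TBI".

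Under Statistical analysis, it treats RASS as categorical and uses it as the example for Fisher's "exact test to compare categorical variables between the study groups (for example, RASS". It gives no time point, category cut, per-patient summary or method for repeated scores. No test is named for ABS.

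The same paragraph treats other graded outcomes differently. For the Extended Glasgow Outcome Scale, "GOSE will be compared using an ordinal approach of sliding dichotomy". QOLIBRI, ventilator-free days and the two length-of-stay measures are analysed like the primary endpoint, that is, by a Wilcoxon rank sum test whose standard error is obtained empirically from the randomization method. Secondary tests are to be adjusted for multiple comparisons; the method is not given.

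**The concern.** The article did not leave the test open. It chose one, and that test fits the endpoint poorly in two ways.

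- **Ordering.** RASS runs along a scale between sedation and agitation. Fisher's test takes the levels as labels, so a shift of many patients by one level in the same direction counts no more than a scatter without direction. In a trial of 40 patients that loss of sensitivity is large.
- **Repetition.** Each patient contributes many scores. Fisher's test needs independent observations, so it can be used only after the scores are reduced to one value per patient. The text does not say that this will be done.

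Agitation is central to the rationale in the Background, and the Discussion says that the study also determines the effect on agitation measures and may supply pilot evidence for a larger trial. A missed or spurious agitation signal would carry into that planning.

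**Working it through.** **The plan's own figure.** The article states no power or error figure for RASS, so the check starts from its sample size, which fixes the number of patients. The inputs are a difference of 450 pg/mL, SD 416 pg/mL, α 0.05 (taken as two-sided) and power 0.9.

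n per arm = 2 × (1.960 + 1.282)² × 416² / 450² ≈ 2 × 10.51 × 0.855 ≈ 18.0

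The t-test version gives 18.97, so 19, as stated. Allowing for 5% early mortality, 19 / 0.95 = 20, which agrees with "our current sample size is 20 patients per arm or a total of 40 patients". The alternatives of 41 per arm (300 pg/mL) and 11 per arm (600 pg/mL) also reproduce. The check below uses 20 per arm.

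**Step 1: power with one value per patient.** Assumptions, none of them from the article: a normal latent score cut into 8 ordered categories; treatment shifts of 0.5, 0.8 and 1.0 SD; 1,000 simulated trials per setting; nominal two-sided 0.05 before any multiplicity adjustment. The cut is at the control-arm median.

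| Shift (SD) | Fisher, all levels | Fisher after cut | Wilcoxon | Loss, all levels | Loss after cut |
|---|---|---|---|---|---|
| 0 (size) | 0.046 | 0.021 | 0.045 | – | – |
| 0.5 | 0.12 | 0.14 | 0.32 | 20 points | 17 points |
| 0.8 | 0.28 | 0.37 | 0.65 | 36 points | 28 points |
| 1.0 | 0.47 | 0.50 | 0.81 | 34 points | 31 points |

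Losses are taken from the unrounded results. A repeat simulation of the cut version gave 0.16 / 0.38 / 0.55 for Fisher and 0.31 / 0.65 / 0.83 for Wilcoxon, so losses of 15, 27 and 28 points. Over both runs and both uses of Fisher the loss is about 15 to 36 points. All three tests keep their size under the null; Fisher after a cut is conservative.

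**Step 2: type I error if scores were pooled.** The RASS window is not stated. If it matched the treatment period ("Both drugs (or double placebos) are administered for 7 days"), there would be 7 × 2 = 14 scores per patient. The within-patient correlation is assumed.

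By formula, the design effect is DE = 1 + (14 − 1) × ICC, and the actual size of a nominal 0.05 test is 2 × [1 − Φ(1.96 / √DE)].

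- ICC 0.1: DE = 2.3, size 0.196
- ICC 0.3: DE = 4.9, size 0.376
- ICC 0.5: DE = 7.5, size 0.474

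The pooled 2 × 2 Fisher test was also simulated, with 10% or 30% of scores agitated and the correlation set on the latent scale. The same latent figure implies a weaker correlation between the yes/no scores, so these sizes are lower than the formula's.

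- Correlation 0: 0.03–0.04
- Correlation 0.1: 0.09–0.12 (repeat run 0.09–0.13)
- Correlation 0.3: 0.20–0.27
- Correlation 0.5: 0.31–0.38 (repeat run 0.30–0.36)

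**Step 3: no pooling.** With one yes/no value per patient (any agitated score), the simulated size of Fisher's test was 0.00–0.025. The inflation in Step 2 comes from pooling alone.

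**The case against.** The best defence is that this is an article. How twice-daily scores become one value per patient is ordinary content of a full analysis plan, and calling RASS categorical fits a single classification per patient at least as well as pooling. On that reading Fisher's test controls type I error. Nor does it require unordered categories: it is valid for ordered ones and simply does not use the order. All of this stands. It removes any claim that the plan as written is invalid. It does not remove the loss of power, because the test itself is stated, and cutting the scale first still costs 15 to 31 points under the assumptions above.

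A reader might infer more than the text supports:

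- **That the trial will pool scores and so produce false positives.** No sentence says this. The count of 14 is borrowed from the dosing period and the correlations are assumed.
- **That one value per patient throws away all but one of the measurements.** It does not if the value is a summary such as the worst score or any agitated score.
- **That ABS has the same fault.** No test is assigned to ABS.
- **That the GOSE analysis is wrong too.** The sliding dichotomy is a cited method. A comparison with a fixed dichotomy would not test it, so nothing is concluded here.

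The planned multiplicity adjustment is no answer to pooling, since it does not correct for correlation within patients.

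**Conclusion.** The concern holds as a poor choice of test for one secondary outcome. With 20 per arm, Fisher's test on RASS gives up roughly 15 to 36 percentage points of power against a rank test, on all levels or after a cut. That range rests on assumed shifts of 0.5 to 1.0 SD, 8 categories and a nominal 0.05. A stricter adjusted level would change the absolute powers.

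The rise in type I error is conditional on pooling. Its size depends heavily on the assumed correlation and on 14 scores per patient, so it is a reason to state the unit of analysis and not evidence of an error in the plan.

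The primary endpoint, its test and the sample size are unaffected. The primary hypothesis concerns catecholamines, heart rate variability and cold pressor response, not agitation. The point is worth correcting because it is cheap, but it does not threaten the trial's main conclusion.

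**What to change.** In Statistical analysis, remove RASS as the example for Fisher's test and state, before unblinding:

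1. **One RASS summary per patient that uses all scores in a stated window**, for example the mean RASS or the proportion of assessments in the agitated range. The choice should follow the question. A mean can offset agitation against sedation; a proportion cuts each score but still gives a graded value per patient. Say how patients with few scores, such as early deaths, are handled.
2. **The test**: the Wilcoxon rank sum test with its standard error taken from the randomization method, as already planned for the primary endpoint, QOLIBRI, ventilator-free days and length of stay. In the check above an ordinary Wilcoxon test on one value per patient had a size of 0.045; the randomization-based version under minimization was not simulated.
3. **A sensitivity analysis**, if wanted: a longitudinal ordinal model of all scores, clustered on patient. With 40 patients it should be kept simple.

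Keep Fisher's test for outcomes that are binary and recorded once per patient.

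The cost is a change of analysis wording. No new data, visits or patients are needed.

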**Figure 1 F1:**
[figure not shown]
**Conceptual model of sympathetic****hyperactivity after severe TBI**.

One strategy to decrease sympathetic hyperactivity is pharmacologic intervention with beta (β)-blockade. Non-selective β-blockade with propranolol, in pre-clinical mouse models, reduces brain edema, improves neurologic outcomes [18], increases cerebral perfusion [19], and decreases cerebral hypoxia [20]. Also, propranolol can reduce the maximum intensity of agitated episodes [14], and even reduces aggressive behavior months after TBI [21,22]. This work has led to two parallel, non-placebo-controlled, open-label, prospective, single-center studies (NCT01202110, NCT01343329), which employ early propranolol after TBI and monitor short-term endpoints, like heart rate [23].

Several retrospective studies [24,25], including two from our group [9,26], have indicated that β-blockade exposure following TBI conveys a 4% to 23% absolute mortality advantage [3]. This mortality benefit is even larger if stratified by early physiological measures of sympathetic excess, such as decreased HRV. Though these findings have resulted in an increase in β-blocker use in our institution from 20% to over 40% in young, severe TBI patients over a 5-year period [9], rigorous prospective evidence regarding the feasibility, outcome benefits and safety of using of β-blockers in TBI patients is lacking.

β-blockade is just one pharmacologic strategy to reduce sympathetic hyperactivity; centrally acting alpha_2_ (α_2_)-agonists also serve as sympatholytic agents [27-29]. The prototypical centrally acting α_2_-agonist, clonidine, decreases plasma catecholamines and improves outcomes in a rat model of incomplete cerebral ischemia [30]. Clinically, clonidine decreases plasma catecholamines and cerebral vasoconstriction without altering cerebral blood flow in patients with severe TBI [31,32].

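### The intention-to-treat rank-sum comparison of ICU stay, hospital stay and QOLIBRI takes no account of death, which can bias length of stay against the arm with fewer deaths and makes QOLIBRI a survivors-only comparison

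*Protocol article*

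**What the plan says.** The Statistical analysis section of the protocol article makes three commitments that bear on this point.

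- Population: "All analyses will occur on an intention to treat basis and will be blinded to treatment assignment".
- Test for the primary endpoint: "we will use a Wilcoxon rank sum test statistic with the standard error determined empirically by the randomization method". The same test is carried over to other outcomes: "QOLIBRI, ventilator-free days, hospital LOS, and ICU LOS are continuous measures that will be analyzed the same as the primary endpoint".
- Death is handled on its own: "Mortality will be studied using Kaplan-Meier analysis and Cox Proportional Hazard Modeling".

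The Study endpoints section lists the in-hospital outcomes side by side as "coma-free days, ventilator-free days, ICU LOS, hospital LOS, and in-hospital mortality", without defining length of stay for a patient who dies. The same section places QOLIBRI at the 3- and 12-month clinic visits.

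The article expects deaths. In the sample size justification, "we assume a 5% early mortality (<1 week) related to critical illness". The Background reports that beta-blocker exposure after TBI "conveys a 4% to 23% absolute mortality advantage" in retrospective studies.

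**The concern.** A stay in the ICU or hospital ends either with discharge alive or with death. A rank test on the number of days treats the two alike, so a patient who dies on day 3 ranks with the shortest stays, which a reader takes as the good end of the scale. If the active arm has fewer deaths, more of its patients remain to accumulate days, and the comparison moves against it. If the active arm has more deaths, the comparison moves in its favour.

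For QOLIBRI the mechanism is different. A patient who has died has no score at all. The only comparison possible without a rule for death is among survivors, a group selected after randomisation. It cannot carry the intention-to-treat label that the section gives to all analyses.

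The trial has 40 patients, and its Discussion says that positive trends would serve as pilot evidence for a larger multicentre trial. The direction of a secondary outcome will therefore be read even when it is not significant.

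**Working it through.** **The plan's own figures.** The article gives no figure for length of stay or QOLIBRI. Its sample size can be reproduced: a two-sided t-test at 0.05 with 90% power, a difference of 450 pg/mL and an SD of 416 pg/mL needs 18.97, so 19 per arm, and 19/0.95 = 20. Nothing below changes that number.

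**Inputs from the article.** 20 patients per arm; 5% mortality in the first week (5% of 20 is one patient per arm); a cited mortality advantage of 4 to 23 percentage points.

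**Assumptions not in the article.** Overall in-hospital mortality is not given, so control mortality is varied from 5% to 30%. For the simulation, survivors' stay is lognormal with median 20 days and log-SD 0.6, and deaths are uniform over days 1 to 7.

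**Step 1: raw length of stay.** Let pC and pA be the proportions dying on control and active. Suppose every death precedes every survivor's discharge and survivors' stays have the same distribution in both arms. Counting ties as half,

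P(active longer) = (1 − pA)·pC + 0.5·(1 − pA)(1 − pC) + 0.5·pA·pC = 0.5 + 0.5·(pC − pA).

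**Step 2: death ranked worst.** The same terms with the sign reversed give P(active worse) = 0.5 − 0.5·(pC − pA).

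**Step 3: numbers.** The last column is the simulated chance, with 20 per arm and 20,000 trials per row, that an ordinary rank-sum test on raw stay is significant in the direction of a longer stay on active. The nominal value is 2.5%, before any multiplicity adjustment.

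| Deaths, control v active | P(active longer), raw | P(active worse), death worst | Significant longer stay, raw |
|---|---|---|---|
| 5% v 5% | 0.50 | 0.50 | 2.6% |
| 5% v 1% | 0.52 | 0.48 | 4.0% |
| 20% v 10% | 0.55 | 0.45 | 7.6% |
| 30% v 7% | 0.615 | 0.385 | 22.7% |

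The probabilities are from the formulas. The simulation agrees closely: 0.613 against 0.615 for raw stay in the last row, where some deaths come after the earliest discharges. At the article's 5%, even with no deaths on active, the shift is at most 0.5 × 0.05 = 0.025.

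**Step 4: what weakens it.** Two departures from the assumptions matter.

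- *Late deaths.* At 25% v 5% mortality the formula gives 0.60. With gamma-distributed stays (mean 20 days, shape 2), it falls to 0.59 when deaths are spread over days 1 to 7, to 0.56 over days 1 to 14, and to 0.51 over days 1 to 30.
- *A shorter stay in survivors.* If treatment shortens survivors' stay by 15%, P(active longer) is 0.447 at 5% v 1%, 0.493 at 20% v 10% and 0.561 at 30% v 7%. In the first two cases raw stay no longer points against treatment.

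**QOLIBRI.** No size can be computed. The article gives neither mortality at 3 or 12 months nor a distribution of scores. The point rests on setting two statements side by side: all analyses are intention to treat, and the outcome is measured at visits that patients who have died cannot attend.

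**The case against.** The strongest reply is that the article never says a death counts as a short stay. It names the outcome and the test, and a full protocol or analysis plan may define stay for patients who die. That is fair as to the definition. But the article does fix the analysis: everyone randomised, a rank-sum test, and mortality kept apart. Carried out as written, it ranks the days as they stand. The point is about that stated method and falls away if a fuller document sets a rule for death.

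Second, the bias may be small here. The only mortality figure is 5% in a week, and patients with impending herniation or expected withdrawal of care are excluded. The 23-point end of the cited range comes from retrospective studies of beta-blockade, not of this combination. Multiplicity adjustment also lowers the false-signal rates. All of this stands, and it limits the size of the bias without removing it.

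Third, mortality is reported and modelled, so a reader can set a difference in stay against it. That helps interpretation but does not correct the test.

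A reader might also infer three stronger things that the document does not support.

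- *That a life-saving treatment would necessarily appear to prolong stay.* It can, but late deaths or a shorter stay in survivors can cancel the effect.
- *That the short-stay mechanism applies to QOLIBRI.* It does not; the problem there is an absent score.
- *That the step from 19 to 20 per arm shows the primary endpoint to be flawed.* That step is ordinary planning for patients without a day-8 sample. Ranking death as the worst norepinephrine level would be a debatable preference, and no criticism of the primary analysis is made here.

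**Conclusion.** The concern holds in a limited form. The fixed rank-sum comparison of ICU and hospital stay can be biased against the arm with fewer deaths. On the probability scale the shift from 0.50 is half the mortality difference: 0.02 at 4 points and about 0.11 at 23 points. This assumes that deaths precede survivors' discharges and that survivors' stays are equal. The mortality levels and stay distributions behind the simulated error rates are assumptions, not figures from the article. Under them, a significant longer stay on active occurs in 4.0% of trials at 5% v 1% mortality and 22.7% at 30% v 7%, against a nominal 2.5%.

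For QOLIBRI, the comparison is restricted to survivors and does not meet the intention-to-treat commitment; its direction and size cannot be stated from the article.

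These are secondary outcomes. The sample size of 40 and the primary analysis are unaffected.

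**What to change.** Keep the rank-sum test with its randomisation-based standard error and state how death enters.

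- **ICU and hospital stay:** give in-hospital deaths the worst rank, tied with one another. Alternatively, analyse ICU-free and hospital-free days over a horizon fixed in advance, with death set to zero.
- **QOLIBRI at 3 and 12 months:** give patients who have died by that visit the worst rank. Survivors who do not or cannot answer are a separate missing-data matter and should not be merged with deaths.
- **Beside these:** report length of stay and QOLIBRI in survivors descriptively, labelled as not a randomised comparison.

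The change is to analysis wording only. In-hospital mortality is already an outcome and long-term deaths are already tracked, so no new data or patients are needed. The price is that each outcome becomes a composite with death, and a difference may reflect mortality rather than days in hospital or quality of life. The survivor description and the separate mortality analysis let the reader see which.
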